**8. Materials**

Questionnaire

The data for this study will be collected using a structured questionnaire that has been developed based on a thorough review of relevant literature on pesticide use and safety practices among agricultural communities in Lebanon and internationally (Abou Ibrahim et al., 2023; Dugger-Webster & LePrevost, 2018; Emery et al., 2015). The questionnaire will consist of four primary sections:

1. **Demographics**: This section will capture participants’ age, gender, years of farming experience, and education level.
2. **Pesticide Practices**: Questions will cover prior training on pesticide safety, pesticide handling practices, types of agricultural environments (open field or greenhouse), and the use of personal protective equipment (PPE). Most questions in this section will be closed-ended.
3. **Knowledge**: This section will measure the participants' awareness of the health risks associated with pesticide use, environmental hazards of pesticides, and the importance of PPE. Responses will be collected using Likert scale questions for a range of agreement or knowledge levels.
4. **Pesticide Label Understanding**: This section will assess participants’ ability to interpret pictograms and color codes on pesticide labels. Due to their complexity, open-ended questions will be used to gauge their comprehension.

The questionnaire will be administered face-to-face by trained surveyors proficient in Arabic to ensure clear communication and facilitate accurate data collection. The surveyors will record responses in real-time using Google Docs, which allows for immediate review to minimize data entry errors. To ensure accessibility for all participants, particularly those with low literacy levels, surveyors will read questions aloud and provide clarification as needed.

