**Randomization**

Participants will be randomly assigned to one of three groups: the Control Group, the Digital Video-Based Learning Group (DVBLG), and the Traditional Educational Session Group (TESG). Each participant’s phone number will serve as their unique identifier, simplifying group allocation and follow-up communication without requiring participants to remember a specific code. To ensure a random allocation, we will use the RAND function in Microsoft Excel.

The process will be as follows:

1. Each participant’s phone number will be entered in a single column in Excel. The RAND function will generate a random number for each participant. These random numbers will then be used to sort the list of participants in ascending order, resulting in a randomized list.
2. Based on this sorted list, participants will be allocated sequentially to each of the three groups, ensuring equal distribution.
3. To facilitate communication, we will create a WhatsApp group for each team. We will use the group to invite the TESG to the educational session, send the educational video to the DVBLG, and provide them with instructions to watch it. Additionally, we will use the group to call them for the post-assessment.

This approach will ensure a transparent and unbiased randomization process, allowing us to assess intervention effectiveness across comparable groups.

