**10. Outcomes**

**Primary Outcome Measures**:

- Ability to correctly identify and interpret FAO pictograms on pesticide labels.
- Knowledge of health risks associated with pesticide use.
- Understanding of the environmental consequences of pesticide misuse.

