**11. Data Collection**

Data will be collected at two time points through face to face interview:

1. Baseline Assessment: Before the intervention, all participants will complete a structured questionnaire assessing their knowledge, practices, and understanding of pesticide safety labels.
2. Post-Intervention Assessment: Following the interventions, participants will complete a post-intervention questionnaire to measure changes in their knowledge and practices.

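### Surveyors may clarify without limit during the open-ended pictogram test, which measures one of three primary outcomes, and the protocol provides no masking of interviewers or scorers

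*Protocol*

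**What the plan says.** Protocol section 8 (Materials, Questionnaire) sets out how the outcome data are obtained. "The questionnaire will be administered face-to-face by trained surveyors proficient in Arabic", and in the same paragraph "surveyors will read questions aloud and provide clarification as needed". The stated reason is access for farmers with low literacy. The permission covers the questionnaire as a whole: no section is exempt, and no script or limit is given. "The surveyors will record responses in real-time using Google Docs", so the person who asks and clarifies also writes down the answer.

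For the section on pictograms and color codes the format is free response: "Due to their complexity, open-ended questions will be used to gauge their comprehension". Section 10 lists three primary outcomes, the first being "Ability to correctly identify and interpret FAO pictograms on pesticide labels". The other two, on health risks and environmental consequences, belong to the Knowledge section, which uses Likert items.

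Section 11 uses face-to-face interviews both at baseline and after the intervention. Under Randomization in section 4, each arm has its own WhatsApp group, and "we will use the group to call them for the post-assessment". The protocol says nothing about masking of surveyors or of those who score answers.

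**The concern.** For a demographic item, clarification is harmless. For an item that asks what a pictogram means, it can turn into the answer, because the meaning is the thing being tested. An instruction to clarify whenever needed leaves it to each surveyor where rewording ends and teaching begins.

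Farmers cannot be masked to whether they attended a session, received a video or received nothing. The main safeguards left against expectation effects are therefore the conduct of the interview and the scoring of the answers. If a surveyor learns the arm, the amount of help given, and the generosity with which a vague answer is written down or judged, may vary with it. Such a difference would enter the between-arm comparison directly. It could inflate the contrast with control, or hide or create a difference between video and session, which is the comparison behind the trial's hypothesis. No analysis can later separate a prompted answer from an unprompted one.

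**Working it through.** The point rests on the text, so the check sets the provisions side by side.

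1. **Does the permission reach a primary outcome?** The clarification sentence in section 8 applies to the whole questionnaire. The label section is part of it and is open-ended. Section 10 makes pictogram interpretation a primary outcome. So yes, for one of three.

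2. **Does it reach the other two?** They are read aloud under the same permission, so help with content is possible there too. Likert items leave no free answer to judge, so the scoring part of the concern does not apply to them. The exposure is smaller in kind.

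3. **Is help limited elsewhere?** The surveyors are described as trained and the questionnaire as structured. Neither word says what help is allowed, and neither makes it equal across arms.

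4. **Can the arm become known at the interview?** The protocol does not say that surveyors hold the allocation. It does say that interviews are face-to-face, that farmers are invited through a group formed by arm, and by design farmers know what they received. A farmer may mention the session or the video. Nothing in the protocol is aimed at preventing this.

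5. **When could help differ by arm?** After the intervention. The baseline questionnaire goes to all participants before any intervention (sections 9 and 11), so teaching through clarification at that point would reach all three arms.

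6. **Can the size be worked out?** It would take the mean shift that clarification produces in one arm relative to another, and the standard deviation of the pictogram score. The protocol gives neither. Its only quantitative target is the 4% to 29% in section 6, which concerns routine label reading. That sample size reproduces, with two-sided 0.05, 80% power, pooled variance and mean proportion (0.04 + 0.29)/2 = 0.165:

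   n = [1.96·√(2·0.165·0.835) + 0.842·√(0.04·0.96 + 0.29·0.71)]² / 0.25² ≈ 33.4, so 34 per group against the stated 35.

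   It describes a different variable on a different scale and cannot calibrate a bias in pictogram scores.

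7. **Does a strict ban on explanation have a cost?** Yes. Section 12 (Handling Missing Data) deletes incomplete cases list-wise. If low-literacy farmers leave more items blank under a stricter rule, they would leave the analysis. The fix has to deal with this.

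**The case against.** The strongest reply is that the natural reading of the sentence is innocent. Trained surveyors, working from a structured questionnaire, help farmers of low literacy to understand the question, not to answer it. That is a fair account of the intention, and it is why reading aloud and some rewording should stay. It does not settle the matter, because the text draws no line between the two kinds of help in the section where the line matters most.

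A second reply is that a scoring key and procedure may stand in a statistical analysis plan that is not at hand. This is accepted: the absence of a key from the protocol is not part of the point. Interviewer conduct and assessor masking are matters of trial conduct that belong in the protocol, and an analysis plan cannot undo prompting.

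Four stronger readings are tempting, and the document does not support them:

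- **That the surveyors are unmasked.** The protocol is silent. It does not say that surveyors belong to the WhatsApp groups, see the allocation list or score the answers.
- **That the primary outcome as a whole is an open-ended test.** It is one of three.
- **That clarification at baseline teaches the control arm in particular.** Any such effect would reach all arms.
- **That the bias could match the effect the trial hopes to find.** This would need invented values for both the shift and the standard deviation.

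**Conclusion.** The point holds as a risk of bias created by a loosely worded instruction. Clarification is unlimited for the open-ended items behind one of the three primary outcomes, no masking of interviewers or scorers is provided, and the arm can readily come to light at the post-assessment. Help with content, and judgement of open answers, could therefore differ by arm. The two knowledge outcomes share the permission to clarify but not the free-response format.

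The size and direction of any bias cannot be derived from the document, and nothing in it shows that bias would occur. The conclusion rests on two assumptions: that no separate surveyor manual limits clarification, and that masking is not arranged somewhere the protocol does not mention. This is a cheap improvement, not a flaw that invalidates the design.

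**What to change.** - **Help during the interview.** Keep reading aloud for everyone. In the Knowledge and Label sections, replace open clarification by re-reading or a scripted neutral rewording of the question, with no explanation of any pictogram, color code or tested term.
- **Recording.** Enter open answers verbatim in the Google Docs form already planned. Enter a non-answer as 'don't know' and score it as not correct, so that list-wise deletion does not remove low-literacy farmers.
- **Scoring.** Have existing team members score the open answers against a written key, with arm and time point hidden.
- **Allocation.** Do not give surveyors the allocation list, and send post-assessment appointments individually instead of through the arm's WhatsApp group.

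The cost is slightly longer interviews and one masked scoring step. Sample, surveyors, questionnaire content and schedule stay as they are. Farmers may still reveal their arm in conversation, so masking at the interview will be imperfect. The scripted wording and masked scoring limit what that can do.

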**Educational Session**

The traditional educational session (TESG) will be delivered in person and will cover critical topics related to pesticide safety. The principal researcher will lead the session, with content validated by experts in plant protection and environmental health. It will involve PowerPoint presentations, visual aids, and interactive discussions on the following topics:

- **Introduction to Pesticides**: Definition, uses, and benefits.
- **Health and Environmental Risks**: An overview of the potential acute and chronic health effects of pesticide exposure and the environmental implications of pesticide misuse.
- **Pesticide Handling and Safety Practices**: This section covers best practices for handling pesticides, with a focus on the importance of PPE use and respect for preharvest intervals.
- **Understanding Pesticide Labels**: This is an explanation of the pictograms and color-coded hazard levels used on pesticide labels based on the Food and Agriculture Organization (FAO) and World Health Organization (WHO) guidelines.

Participants can ask questions and share their experiences with pesticide use. The session aims to create a supportive learning environment where farmers can engage with the material actively. Additionally, participants in the TESG group will be encouraged to apply what they’ve learned in their daily practices.

**Educational Video**

The Digital Video-Based Learning Group (DVBLG) will receive an educational video via WhatsApp. The video is approximately 4 minutes long and covers the same core content as the traditional educational session. Key features of the video include:

- **Concise Content**: The video presents information on pesticide risks, safe handling practices, label interpretation, and PPE usage in a straightforward and easily digestible format.
- **Visual Aids**: Animated visual aids and examples are incorporated to help farmers understand complex concepts, such as interpreting pesticide pictograms and color codes, enhancing their retention of the information.
- **Arabic voice-over**: The video includes a clear and engaging Arabic voice-over, ensuring it is accessible to all participants.
- **Reinforcement Mechanisms**: The short length and availability via WhatsApp allow participants to re-watch the video as needed, reinforcing their understanding over time.

A multidisciplinary team, including experts in agricultural safety and public health, developed and reviewed the video content to ensure it is relevant and culturally appropriate for the target audience.

**9. Timeline:**

| **Time point** | **Study period** | **Enrolment** | **Allocation** | **Intervention** | **Post- Intervention Assessment** |
| --- | --- | --- | --- | --- | --- |
| **June 10- June 30, 2024** | Recruitment | Eligibility screening |  |  |  |
| **July 1- July 21, 2024** | Baseline Assessment | Informed consent, Baseline data collection | Randomization |  |  |
| **July 22- August 9, 2024** | Intervention and Assessment |  |  | Intervention sessions (TESG and DVBLG) | Post-intervention assessment |

**10. Outcomes**

**Primary Outcome Measures**:

- Ability to correctly identify and interpret FAO pictograms on pesticide labels.
- Knowledge of health risks associated with pesticide use.
- Understanding of the environmental consequences of pesticide misuse.

**Secondary Outcome Measures**:

- Awareness of the importance of personal protective equipment (PPE) usage.
- Reported changes in pesticide handling practices and PPE compliance.

**11. Data Collection**

Data will be collected at two time points through face to face interview:

1. Baseline Assessment: Before the intervention, all participants will complete a structured questionnaire assessing their knowledge, practices, and understanding of pesticide safety labels.
2. Post-Intervention Assessment: Following the interventions, participants will complete a post-intervention questionnaire to measure changes in their knowledge and practices.

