**Participants recruitment:**

Participants for this study will be recruited from a list of 418 agricultural farmers provided by the municipalities of three nearby coastal villages in the Akkar Governorate, northern Lebanon. These farmers are registered in the municipal database, making them eligible for recruitment in the study due to their involvement in agriculture within this region. Systematic sampling will be used, whereby every third farmer on the list will be contacted to determine eligibility and interest in participating.

To qualify, participants must be at least 18 years old, engaged in agricultural activities within the coastal area, actively using chemical pesticides, and have access to WhatsApp on a personal or family member's device. Farmers meeting these criteria will be informed about the study’s objectives, procedures, and voluntary nature, emphasizing confidentiality and the right to withdraw at any time. Consent will be obtained through signatures or fingerprints, depending on literacy levels. Farmers who are not eligible or choose not to participate will be replaced by the next farmer on the list, and this process will continue until the required sample size of 150 participants is reached.

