**6. Sample Size Calculation**

The sample size calculation for this randomized controlled trial will be based on prior data from a cross-sectional study conducted in the same region, which found that only 4% of farmers routinely read pesticide labels before preparing pesticide mixtures. To achieve a statistically meaningful improvement with our educational intervention, we aim to detect an increase in this behavior by 25%—raising it from 4% to 29%.

Using a significance level of 0.05 and a power of 80%, we estimate that each group (Digital Video-Based Learning Group, Traditional Educational Session Group, and Control Group) will require approximately 35 participants, totaling 105 participants across the three groups. However, we plan to recruit additional participants to account for potential attrition and ensure a robust final sample. The number of these additional participants will be determined based on observed participation and retention rates during the recruitment phase, allowing us to meet our target sample size despite potential dropouts. This approach will help maintain sufficient statistical power throughout the study, even if some participants cannot complete all stages.

7. **Description of the interventions.**

This randomized controlled trial will involve three distinct groups, each receiving different levels of intervention:

1. **Control Group (CG)**
   Participants in the control group will receive no educational intervention and will serve as a baseline to compare the effects of the other interventions. This group will only participate in baseline and follow-up assessments to measure changes in knowledge, practices, and understanding of pesticide labels without external educational support.
2. **Digital Video-Based Learning Group (DVBLG)**

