   The participants in this group will receive a 4-minute educational video on pesticide safety distributed via WhatsApp. The video will cover essential topics on pesticide use, focusing on reading pesticide labels, understanding FAO pictograms, interpreting color codes, and practicing safe handling procedures, including using personal protective equipment (PPE). Visual aids and examples will be incorporated into the video to enhance comprehension, and the content will be presented in Arabic to ensure clarity and accessibility. The video will be available for rewatching, allowing flexible, self-paced learning. Participants in this group will receive a transportation fee as an incentive for participating.
3. **Traditional Educational Session Group (TESG)**
   Participants in the traditional educational session group will attend an in-person, interactive training session. This session, led by the primary researcher with support from a plant protection specialist and an environmental health professor, will use PowerPoint presentations and encourage group discussions. Topics covered will mirror those in the video, including pesticide safety, label interpretation, pictograms, color coding, and PPE usage. The face-to-face format will allow for immediate questions, personalized guidance, and opportunities for farmers to share their experiences. The session will take place in the Safadi Foundation’s conference room in Der Dalloum, Akkar, with participants receiving transportation fees and breakfast as incentives.

Each intervention is designed to improve the participants' knowledge, practices, and interpretation of pesticide safety labels, with the goal of assessing which format—digital or traditional—is more effective in a resource-limited setting. The interventions are specifically crafted to address language and literacy barriers, ensuring accessible and practical education for the farmers involved.

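### Farmers from neighbouring villages are individually randomised to a forwardable video, but no record of receipt is described although the per-protocol primary analysis needs one

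*Protocol*

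**What the plan says.** - **Who is randomised.** Participants come from a list of 418 farmers "provided by the municipalities of three nearby coastal villages in the Akkar Governorate" (Protocol, section 5, recruitment). They are allocated individually from one randomly sorted list (section 4, Randomization). Nothing keeps a village or household in one arm.
- **How the video travels.** It is sent through the video arm's WhatsApp group with an instruction to watch it. Section 7 adds: "The video will be available for rewatching, allowing flexible, self-paced learning". WhatsApp access is required of every participant, including controls, and may be on a relative's phone (section 5).
- **Controls.** They are assessed only, to measure change in knowledge, practices and "understanding of pesticide labels without external educational support" (section 7).
- **What is asked.** The nearest questionnaire item is background: "Questions will cover prior training on pesticide safety" (section 8). After the interventions, "Following the interventions, participants will complete a post-intervention questionnaire to measure changes in their knowledge and practices" (section 11).
- **Analysis.** Section 12 takes a per-protocol approach to the primary outcomes and does not say what counts as having received an intervention. The hypothesis is that the video is as effective as the session. No margin is given, and the comparison is by one-way ANOVA with post hoc tests.

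**The concern.** The video lasts four minutes and can be forwarded in seconds. If 133 farmers are enrolled, 133/418 = 32% of the listed farmers are in the trial, spread over three arms in the same villages. A control who is sent the video counts as untaught, and a video-arm farmer who never opens it counts as taught.

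Two things are at stake. Exposure of controls shrinks both differences from control. And as described, adherence could not be established for the video or control arms, although the primary analysis depends on it. There is one post-assessment, in the same 22 July to 9 August window as the interventions, so viewing and sharing not asked about then are unlikely to be recovered reliably. A later SAP cannot supply data that were never collected.

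**Working it through.** **Inputs from the protocol.** Section 6: "Using a significance level of 0.05 and a power of 80"%, an increase in routine label reading "raising it from 4% to 29"%, and each group "will require approximately 35 participants, totaling 105 participants across the three groups". Enrolment is 133 (section 5, about 133/3 = 44 per arm); the recruitment text gives 150 (50 per arm). **Assumptions.** Two-sided test, since sidedness is not stated. A share c of controls sees the video and gains its full effect. No attrition. The protocol gives no value for c.

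**1. The plan's own figure.** With p1 = 0.04, p2 = 0.29 and mean p̄ = 0.165:

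n = [1.960·√(2p̄(1−p̄)) + 0.842·√(p1(1−p1) + p2(1−p2))]² / (p2−p1)²

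= [1.960 × 0.5249 + 0.842 × 0.4943]² / 0.25² = 33.4, so 34 per arm. The stated 35 is reproduced. It contains no allowance for contamination.

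**2. Dilution against control.** The control rate becomes 0.04 + 0.25c, and

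power = Φ{[(p2−p1)√n − 1.960·√(2p̄(1−p̄))] / √(p1(1−p1) + p2(1−p2))}.

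For c = 20% and n = 44: p1 = 0.09, p̄ = 0.19, and (0.20 × 6.633 − 1.960 × 0.5548)/0.5365 = 0.446, so power is 67%.

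| Controls seeing video | Control rate vs 29% | Power, 35 per arm | Power, 44 per arm | Power, 50 per arm |
|---|---|---|---|---|
| 0% | 4.0% | 82% | 90% | 93% |
| 10% | 6.5% | 70% | 80% | 85% |
| 20% | 9.0% | 57% | 67% | 73% |
| 30% | 11.5% | 44% | 53% | 59% |

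Enrolling 133 absorbs exposure of about 10% of controls and no more. The table uses the sizing endpoint, which is not itself among the listed primary outcomes, so it shows scale only.

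**3. Direction for video versus session.** Suppose, for illustration, that the session adds 25 points and the video 16, a true gap of 9.

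- 20% of session farmers miss the session and see only the video: 0.8 × 25 + 0.2 × 16 − 16 = 7.2. The gap narrows.
- 30% of session attenders also see the video, with no added benefit: 25 − 16 = 9. Unchanged.
- The same 30% gain 5 extra points: 25 + 0.3 × 5 − 16 = 10.5. The gap widens.
- 20% of the video arm never watch: 25 − 0.8 × 16 = 12.2. The gap widens.

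**4. Where true switching does occur.** At 44 per arm, an unadjusted two-sample comparison of a true 0.6 SD difference has power Φ(0.6 × √22 − 1.960) = 80%. If 20% switch in each direction, the difference becomes 0.6 × (1 − 0.4) = 0.36 SD and power is 39%. This is one pattern among those in step 3.

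**The case against.** - **Direction.** A reader might infer that cross-exposure necessarily pushes video versus session towards equality and so favours the trial's hypothesis. The documents do not support that. Content is meant to be the same in both formats, so a session attender who also sees the video may leave the gap unchanged or widen it, and unopened videos can widen it too. Only some patterns bring the arms together. What stands is that the patterns could not be told apart.
- **Absence.** A reader might also infer that nobody will be asked about exposure. The questionnaire is summarised by section and its items are not shown, so the supportable statement is that no such item is described. Session attendance is observable on the day, but no log is mentioned.
- **The control-group sentence.** It describes what controls are given. It need not be read as an assumption that nothing reaches them.
- **Size.** Planned enrolment exceeds 105, and the window of about 19 days limits spread. Starting from exactly 80% power would overstate the loss at 44 per arm. Conversely, part of the surplus is meant for attrition, so the 44-per-arm column is favourable to the plan.
- **Generic risk.** Cross-exposure threatens any individually randomised education trial, and no two passages conflict over it. That is true, but the per-protocol primary analysis makes receipt data a requirement of this plan.

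**Conclusion.** The point holds as a gap in data collection that the planned analysis exposes. Dilution of both contrasts with control is neither prevented nor detectable from what is described, and the per-protocol set cannot be determined for the video and control arms. For video versus session the bias has no known direction, so a non-significant difference, with no margin stated, could not safely be taken to show equal effectiveness.

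Under the assumptions listed in the check, exposure of 10% to 30% of controls costs about 10 to 37 percentage points of power at 44 per arm (90% to between 80% and 53%). The actual rate is unknown and could be small. This is a cheap improvement that should be made; it does not invalidate the design.

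**What to change.** - **Section 4, Randomization (WhatsApp groups):** ask participants not to forward or share study material until the last post-assessment is done, and log attendance at the session.
- **Sections 8 and 11:** add two or three closed questions in all three arms, placed after the knowledge and label items so that they do not prompt answers: watched the study video (not at all, partly, fully); attended the session; received study material or its content from another participant or a household member.
- **Section 12:** make the as-randomised comparison primary and report receipt by arm beside it. Use the exposure answers only in a secondary per-protocol or sensitivity analysis. They should not be used to exclude participants from the primary analysis, because dropping exposed controls or non-viewers after randomisation would introduce selection bias.

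The cost is about a minute per interview, one line in a message and an attendance sheet. Receipt will be self-reported and so imperfect. Allocation and sample size are unchanged.
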